### Outcome measures

2.7

The primary outcomes and secondary outcomes will be collected in 4 time points: before intervention, 1 month after intervention, 3 month after intervention, 6 month after intervention. All variables will be measured in both experiment group and control group.

### Primary outcome measures

2.8

Kinesiophobia: The tampa scale for kinesiophobia for temporomandibular disorders (TSK-TMD) was developed by Visscher in 2010,^[21]^ and introduced to china by He et al to measure the status of kinesiophobia in TMD patients in 2016.^[38]^ The scale has 12 items and 2 dimensions, including activity avoidance and somatic focus. The scale uses the Likert 4-level scoring method, ranging from 1 (strongly disagree) to 4 (strongly agree), and the score ranges from 12 to 48 points. The high score indicates the high level of kinesiophobia. The Cronbach's α coefficient of the Chinese version of the scale is 0.919, and the Cronbach's α coefficients of the two dimensions are 0.895 and 0.907.^[38]^

OHRQOL: The oral health impact scale for patients with temporomandibular disorders (OHIP-TMDs) is a specific tool used to assess the OHRQOL of TMD patients.^[39]^ The Chinese version of the OHIP-TMDs was introduced by He et al in 2016.^[40]^ The scale consists 22 items, including 7 dimensions. Each item has 5 options, ranging from 0 (almost none) to 4 (very frequent), and the OHRQOL of TMD patients is evaluated from the aspects of limited function, physical pain, psychological discomfort, physical disorder, psychological disorder, social disorder, disability. The Cronbach's α coefficient of the Chinese version of OHIP-TMDs is 0.917, and the test-retest reliability is 0.899.^[40]^

### Secondary outcome measures

2.9

Pain intensity: The numerical rating scale (NRS) is used for measurement.^[41]^ The scale divides a straight line into 10 parts, and uses the numbers 0–10 at each point to indicate the degree of progressive increase in pain, 0 means no pain and 10 means severe pain, Patients score themselves.^[42]^

Self-efficacy: The general self-efficacy scale (GSES) is a commonly used measurement tool to assess general self-efficacy.^[43]^ The GSES is single-dimensional, including a total of 10 items. It uses the Likert 4-level scoring method, ranging from 1 (completely incorrect) to 4 (completely correct), corresponding to 1 to 4 points. Total scores for the scale range from 10 to 40 points, where higher scores indicate higher self-efficacy. The Cronbach α coefficient of the Chinese version of the GSES is 0.87.^[44]^

Pain catastrophizing: Pain Catastrophizing is evaluated by pain catastrophizing scale (PCS), which is one of the most commonly used measurements with good reliability.^[45,46]^ It consists of 13 items with three dimensions: contemplation, magnification, and helplessness. Each item has 5 options, from 0 (not at all) to 4 (all the time). Total scores for the scale range from 13 to 52 points, where higher scores indicate higher pain catastrophizing. The effectiveness and reliability of PCS have been widely described in clinical and non-clinical samples.^[45]^

Anxiety and depression: Anxiety and depression are measured by the hospital anxiety and depression scale (HADS).^[47]^ The scale includes two subscales, for anxiety and depression, with 7 questions each. Each question includes 4 options, ranging from 0 to 3 points. The scores of the anxiety and depression subscales are divided into: 0–7 for asymptomatic, 8–10 for suspicious symptoms, and 11–21 for certain symptoms. When point ≥ 8 points, including suspicious and symptomatic, symptoms are all considered positive. The Cronbach α coefficient of the Chinese version is 0.762 and 0.787 respectively, indicating good reliability.^[48]^

### Demographic information and clinical measurements

2.10

The study will use a self-designed general questionnaire, including general demographic information and clinical measurements. General demographic information includes the patient's sex, age, education level, and income level; The clinical measurements includes maximum mouth opening, joint noise, joint trauma, joint locking, mouth opening limitation, etc. The clinical measurements will be filled out by checking the patient's case book.

### Sample size calculation

2.11

The sample size of this trial was based on the kinesiophoia score. Based on the previous research results of our research group, the mean of kinesiophobia was 34.37, with a standard deviation (SD) of 6.96 points.^[29]^ To achieve 90% power with a significant level of 0.05, a minimum of 90 patients is needed. Considering the possibility of withdrawal and loss of follow-up, the sample size was expanded by 20%, and the final sample size was determined to be 108 participants, with 54 participants in the experiment group and 54 participants in the control group. Sample Size was performed by using PASS Software (version 14.0; NCSS Statistical Software, Kaysville, UT) (http://www.ncss.com/software/pass/).

### Patient recruitment

2.12

Recruitment for the study will begin in November 2020 and is expected to be completed in January 2020. Information about the purpose and process of the study will be provided orally by the researcher. The participants can ask questions or doubts about any aspect of the study. The investigator will provide participants with a guarantee of data confidentiality. The informed consent includes the background and purpose of the study, therapeutic interventions, research findings, and expected strengths and weaknesses.

### Randomization and blinding

2.13

The randomization of this study will be carried out by researchers who are not involved in recruitment. Participants will be grouped by the random number table method. Items assigned will be hidden and sealed in an opaque envelope in sequential numbered order. Participants will be randomly assigned to experiment group and control group. Before random allocation, they don’t know which treatment they would receive (Fig. 2).

**Figure 2 F2:**
[figure not shown]
Study design.

### Data management

2.14

The participants fill out questionnaires, and the information will be input into Excel for statistical analysis. None of the participants’ names are exposed during the study. All data in the trial will be stored in the computer and encrypted. Participants’ informed consent will be kept by the researcher.

### Statistical analysis

2.15

SPSS21.0 software (IBM Corp., Armonk, NY) will be used to perform all statistical analysis. Continuous variables are described as the mean and standard deviation, and categorical variables are presented by percentages (%) and absolute (n) frequencies. In order to determine whether the parameters are suitable for statistical analysis, the normality test is firstly performed. Student's *t* test or chi-square test was to compare baseline data. Repeated-measures analysis of covariance (ANOVA) will be used to evaluate the effect of intervention on primary outcomes and secondary outcomes. *P < *.05 is considered statistically significant. Finally, the possible loss or withdrawal will be statistically analyzed according to the treatment intention.

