**Methods::**

A total of 108 individuals between 18 and 65 years of age, who will be referred to the temporomandibular joint clinic of Stomatology Hospital of Tianjin Medical University in china will be randomized into 2 treatment arms. The control group will receive a conventional treatment, whereas the experiment group will receive CBT on the basis of the control group. The primary outcomes will be the kinesiophobia and OHRQOL, and will be measured by the Tampa scale for kinesiophobia for patients with Temporomandibular Disorders (TSK-TMD) and the Oral Health Impact Scale for patients with temporomandibular disorders (OHIP-TMDs), the secondary outcomes will be pain intensity measured by Numerical Rating Scale (NRS), pain catastrophizing measured by Pain Catastrophizing Scale (PCS), anxiety and depression measured by Hospital Anxiety and Depression Scale (HADS), and self-efficacy measured by General Self-Efficacy Scale (GSES).

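### Two co-equal primary outcomes are each tested at an unadjusted P < .05 with no success rule and no named deciding term; if either suffices, the trial-wide false-positive rate is about 7–10%.

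*Protocol article*

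**What the plan says.** - **Outcomes.** The Abstract states "The primary outcomes will be the kinesiophobia and OHRQOL". The Introduction, section 2.8 and the Discussion also treat the two as equals.
- **Visits.** Section 2.7 collects every outcome at four times: "before intervention, 1 month after intervention, 3 month after intervention, 6 month after intervention". None is marked as primary.
- **Analysis.** Section 2.15 states "Repeated-measures analysis of covariance (ANOVA) will be used to evaluate the effect of intervention on primary outcomes and secondary outcomes" and then sets one significance threshold, P < .05. It gives no adjustment, order of testing or success rule, and names no model term as decisive. The model is called both an analysis of covariance and an ANOVA.
- **Sample size.** Section 2.11 states "The sample size of this trial was based on the kinesiophoia score" and "To achieve 90% power with a significant level of 0.05, a minimum of 90 patients is needed". It gives no variance, difference or power for OHIP-TMDs.

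**The concern.** A trial with two primary outcomes has to say what counts as success. One significant scale and two significant scales are different claims, with different error rates and different power. The article sets the threshold and the two outcomes but not the rule that joins them.

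A repeated-measures model also yields at least two between-arm results per outcome: the group term, and the group × time term. Which one carries the treatment effect depends partly on whether baseline enters as a covariate or as one of the repeated levels, and the double label of the model does not settle that.

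If a positive result on either scale, or on either term, may be called a positive trial, the nominal 5% does not hold for the claim that CBT works, and the choice could be made after the data are seen. If both scales are needed, the sample size has been justified for only one of them.

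**Working it through.** **Inputs from the article:** two primaries (Abstract); alpha 0.05 (sections 2.11 and 2.15); 90% power, N = 90, hence 45 per arm, and SD 6.96 (section 2.11); 75.2% of the variance in OHRQOL explained by kinesiophobia (Introduction).

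**Assumptions:** tests are two-sided. The correlation r between the two test statistics lies between 0 and 0.87, where √0.752 = 0.867 reads the 75.2% as a simple R².

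**1. The plan's own figure.** N = 90 cannot be reproduced, because no between-arm difference is given. Solving backwards with the normal approximation:

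difference = SD × (1.960 + 1.282) × √(2/45) = 6.96 × 3.2415 × 0.2108 = 4.76 points (0.68 SD).

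This uses the full 0.05 for TSK-TMD and leaves none for a second primary.

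**2. Either primary suffices, one term each.** If the tests are independent, the error is 1 − 0.95² = 9.75%. For correlated tests it is P(|Z₁| > 1.96 or |Z₂| > 1.96) from the bivariate normal:

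| r | Error |
|---|---|
| 0 | 9.75% |
| 0.5 | 9.1% |
| 0.87 | 7.3% |

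Simulating the group × time test under the null (20,000 trials, 45 per arm, four visits, assumed within-patient correlation 0.6) gave 9.5%, 9.0% and 7.5%, which agrees.

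**3. Either primary, and either the group or the group × time term.** The same simulation gave 18.0% at r = 0, 17.3% at r = 0.5 and 14.0% at r = 0.87.

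**4. Both primaries required, one term each.** The error is at most 5% under any null. When both nulls are true, it is 0.25% (r = 0) to 2.7% (r = 0.87). Power is then the question. If OHIP-TMDs is assumed also to have 90% power, joint power is 0.9 × 0.9 = 81% at r = 0 and 86% at r = 0.87. The article does not support that 90% for OHIP-TMDs, so these figures are illustrative.

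**5. Splitting alpha.** At 0.025 and the back-solved 4.76 points, power with 45 per arm is Φ(3.2415 − 2.2414) = Φ(1.000) = 84%. Regaining 90% takes 45 × [(2.2414 + 1.2816)/3.2415]² = 53.2, so 54 evaluable per arm. That equals the planned enrolment of 54 per arm and leaves no allowance for loss.

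**The case against.** The strongest reply is that a condensed article need not carry the multiplicity procedure, and that P < .05 is a reporting convention rather than a decision rule. In part this stands: silence on a primary visit, taken alone, would be no finding. But the article does more than stay silent. It fixes two equal primaries, states one unadjusted threshold for them, and sizes the trial on one of them at the full 0.05. A later analysis plan would have to reconcile these statements.

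A reader might go further and infer six primary tests (two scales at three follow-ups), with an error of 14–24% under assumed correlations. The article does not support that. Section 2.15 puts all visits of an outcome into one repeated-measures model and plans no separate test at each month.

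A reader might also conclude that the error rate is shown to be well above 5%. That does not follow either. Without a success rule the rate is undefined, and requiring both scales on one term each would hold it at 5% with no adjustment.

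Nor do the documents point to month 6 as the deciding visit. The Discussion's remark on duration of effect concerns earlier CBT studies, most with pain as the primary outcome, and a single late contrast may be less precise than a group effect pooled over visits.

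**Conclusion.** The concern holds in a bounded form. As written, the plan does not secure both 5% error and 90% power for a claim resting on two primaries:

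- **Either scale, one term each:** about 7–10% error.
- **Either scale, group or group × time:** about 14–18%.
- **Both scales, one term each:** at most 5% error, with the 90% power established for kinesiophobia only.

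The figures rest on two-sided tests, and the 14–18% also on the assumed within-patient correlation of 0.6. The lower ends rest on r = 0.87. If other predictors contributed to the 75.2%, or if the scales correlate less in this sample, the error moves towards the upper ends.

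**What to change.** In section 2.15, before outcome data are seen:

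1. Name one between-arm term or contrast of the repeated-measures model as decisive for each primary. Whether that is a single month or a pooled effect is for the sponsor to choose.
2. Test TSK-TMD, the outcome the trial is sized on, first at two-sided .05. Test OHIP-TMDs at .05 only if TSK-TMD is significant. This order keeps the trial-wide error for the two primaries at or below 5%.
3. Label all other terms, visits and secondary scales as supportive, with estimates and confidence intervals.

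**Cost:** a few sentences, no added patients, and no alpha taken from TSK-TMD. The downside is that OHIP-TMDs cannot be claimed if TSK-TMD fails.

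If the sponsor wants the two scales to stay equal, there are two alternatives:

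- **Holm.** Restate the power: about 84% for TSK-TMD when tested at 0.025 with 45 per arm. Keeping 90% needs 108 evaluable patients, so enrolment of 130 by the article's own 20% expansion (108 × 1.2 = 129.6), or 135 if 20% are actually lost (108/0.8).
- **Require both.** No alpha adjustment is needed, but state that the 90% applies to kinesiophobia only.

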In previous studies, the efficacy of CBT in TMD patients has been explored, but most of these studies use pain intensity as a primary outcome, the duration of the effect has not been determined. The reason may be that there are great differences in CBT studies for TMD patients, including specific techniques, different background of the implementers, treatment frequency, treatment time, observation time after treatment, etc.^[51–55]^ In the study of the effectiveness of CBT alone, Mishra et al^[56]^ reported that patients in the CBT group had lower pain intensity compared to the non-treatment group, Gardea et al^[57]^ also reached the same conclusion. Dworkin et al^[52]^ reported that after 6 courses of CBT treatment, the patient's pain did not significantly improve compared with the conventional treatment group. Mishra et al^[56]^ performed more frequent CBT (12 courses of treatment) on patients without any mental disorders, and the pain intensity was significantly reduced. Tuner et al^[34]^ showed that CBT significantly improved the pain intensity in the 12-month follow-up, but haven’t been improved in the 8-week follow-up. These indicate that the intervention time and follow-up time need to be considered in the process of CBT.^[34,55]^

Through literature review, we found that the previous protocols of CBT mainly focused on the improvement of the negative emotions, such as anxiety, depression, and pain management, whereas our study focus on improving the patient's kinesiophobia, with the goal of improving patients’ quality of life. We correct the patient's poor cognition of the fear of mandibular movement, so that the patient can actively treat and exit the cycle of false cognition.

In addition, considering that the ability of CBT implementers may affect the patient's prognosis, the implementers of our research team will be trained by psychotherapists before the intervention. It will be carried out under the premise of comprehensively considering the patient's psychological status, disease severity, and treatment frequency.

To enhance the reliability of the results, methodological factors will be considered in our study. Taking the possible absence and withdrawal of the subjects into consideration, the sample size has been increased by 20%. If there is any missing or withdrawal of the participants, statistical analysis will be conducted according to the research protocol and intention-to-treat analysis.

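### The named repeated-measures method joins two different models and, in its standard form, analyses only complete cases, against the stated intention-to-treat promise

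*Protocol article*

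**What the plan says.** The protocol article gives a single analysis for all primary and secondary outcomes (2.15, Statistical analysis): "Repeated-measures analysis of covariance (ANOVA) will be used to evaluate the effect of intervention on primary outcomes and secondary outcomes". On software it says: "SPSS21.0 software (IBM Corp., Armonk, NY) will be used to perform all statistical analysis". It names no procedure within that package. The section closes with: "Finally, the possible loss or withdrawal will be statistically analyzed according to the treatment intention". The Discussion repeats the promise: "If there is any missing or withdrawal of the participants, statistical analysis will be conducted according to the research protocol and intention-to-treat analysis".

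Outcome measures (2.7) has the scores "collected in 4 time points: before intervention, 1 month after intervention, 3 month after intervention, 6 month after intervention". Sample size calculation (2.11) rests on the kinesiophobia score: "the mean of kinesiophobia was 34.37, with a standard deviation (SD) of 6.96 points". It asks for 90 patients for 90% power at 0.05 and adds 20% for withdrawal and loss, giving 108 (54 per arm). The article does not state the role of the baseline score, the effect to be tested or the time point that decides the trial.

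**The concern.** There are two problems on the face of the text.

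- **The name does not fix a model.** Analysis of covariance and ANOVA differ in whether a covariate is used. Here the difference decides whether the baseline score is adjusted for or enters as the first of four repeated measurements.
- **The method and the promise pull apart.** Repeated-measures ANOVA or ANCOVA in its standard form needs a complete row for each participant. Under either reading, a participant who misses one of the three follow-ups leaves the analysis. Intention to treat is offered as the answer to loss and withdrawal, but it is a rule about who is analysed and in which arm. It does not produce the missing scores.

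At stake is the randomised comparison for both primary outcomes. If those who miss visits differ between arms in ways related to their scores, the completers are no longer comparable. An unfixed model also leaves the analysis and the analysed population open to choice after the data are seen.

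**Working it through.** **Inputs from the article:** SD 6.96, alpha 0.05, power 90%, 90 patients expanded by 20% to 108, 54 per arm, and measurements at baseline, 1, 3 and 6 months. **Assumed, because not stated:** two-sided alpha, equal SDs, compound symmetry with between-visit correlation ρ of 0.3 to 0.7, missingness completely at random in steps 2 and 3, and the between-group difference.

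**Step 1. The plan's own figure.** 90 × 1.20 = 108 reproduces. The 90 cannot be reproduced, because one mean and one SD are given and no difference. Solving backwards for 45 per arm:

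δ = SD × √(2/n) × (z₀.₉₇₅ + z₀.₉₀) = 6.96 × √(2/45) × (1.960 + 1.282) = 4.76 points (0.68 SD).

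**Step 2. When complete rows fall below 90.** Total loss: 1 − 90/108 = 16.7%. If each of the three follow-ups is missed independently with probability m, the complete fraction is (1 − m)³. Setting (1 − m)³ = 90/108 gives m = 1 − (5/6)^(1/3) = 5.9%.

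**Step 3. Effect on a single-visit comparison at 4.76 points.** Power = Φ(δ / (SD√(2/n)) − 1.96), with n = 54(1 − m)³ for complete rows and n = 54(1 − m) for everyone seen at that visit.

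| Missed per visit | Complete rows of 108 | Power | Seen at the visit | Power |
|---|---|---|---|---|
| 5% | 92.6 | 0.91 | 102.6 | 0.93 |
| 10% | 78.7 | 0.86 | 97.2 | 0.92 |
| 15% | 66.3 | 0.80 | 91.8 | 0.91 |
| 20% | 55.3 | 0.72 | 86.4 | 0.89 |

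With pure dropout and no intermittent misses the loss is milder: 20% leaves 86.4 completers (power 0.89) and 30% leaves 75.6 (0.84).

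**Step 4. If baseline is a repeated level.** With a constant effect d after baseline, the group main effect is (0 + d + d + d)/4 = 0.75d, so 4.76 becomes 3.57. With n per arm:

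- group main effect: the participant mean has variance SD²(1 + 3ρ)/4;
- group-by-time, 3 df: noncentrality (n/2) × 0.75d² / (SD²(1 − ρ));
- baseline-adjusted average of the follow-ups: variance SD²((1 + 2ρ)/3 − ρ²).

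Power with 45 per arm and complete data:

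| Effect, ρ | Group main effect | Group-by-time | Baseline-adjusted average |
|---|---|---|---|
| 4.76, 0.3 | 0.94 | 0.81 | 0.998 |
| 4.76, 0.5 | 0.86 | 0.93 | 0.999 |
| 4.76, 0.7 | 0.78 | 0.995 | 1.00 |
| 3, 0.5 | 0.48 | 0.53 | 0.88 |
| 3, 0.7 | 0.41 | 0.77 | 0.95 |

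**Step 5. Bias, illustration only.** In simulated trials with no true effect and dropout made to depend on arm and an earlier score, a complete-case comparison at 6 months, even when baseline-adjusted, was off by about 0.7 to 0.8 points with about 9% false positives. A likelihood model using all available scores had about zero bias and about 5%. The dropout mechanism is invented, so the direction carries over but the size does not.

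**The case against.** The strongest reply is that a condensed article need not describe missing-data handling, and that the full protocol or analysis plan may name imputation or a mixed model. That is fair, and no finding rests on the absence of an imputation rule. What remains is what the article does state: a self-contradictory method name, and a method whose standard form conflicts with the promise beside it.

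Several stronger readings are tempting and are not supported:

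- **That baseline is treated as an outcome.** Outcome measures lists collection times, not model levels, and the words analysis of covariance point, if anywhere, to a covariate. The three-quarters dilution holds only under the other reading.
- **That the software drops everyone with a missed visit.** This is true of the SPSS GLM repeated-measures procedure. The article does not name a procedure, and SPSS MIXED keeps partial records.
- **That the plan cannot deliver intention to treat.** Imputation before the analysis, or a mixed model, would allow it. The plan does not deliver it as worded.
- **That power is certainly lost.** At 4.76 points the group-by-time test ranges from 0.81 to 0.995. With 20% random dropout, a 3-point effect and ρ of 0.5/0.7, keeping partial records raised 6-month power only from 61%/78% to 63%/80%. Much of the gap in step 4 comes from the effect tested, not from dropped participants.
- **That the plan allows for a fifth being lost.** The 20% expansion covers a sixth.
- **That the Discussion adds a per-protocol analysis.** Its words can equally mean as the protocol sets out, so nothing is built on them.

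**Conclusion.** The concern holds in a limited form. The named method does not identify one model. In its standard form under either reading it is a complete-case analysis, and nothing in the article reconciles that with the intention-to-treat promise made in the Statistical analysis section and again in the Discussion.

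The firm figure is the threshold: below 90 completers once total loss passes 16.7%. With independent misses the same threshold is 5.9% per follow-up. The fall in power (for example 0.86 against 0.92 at 10% missed per visit) rests on the back-calculated 4.76-point difference, two-sided alpha and random missingness. The dilution to 0.75 of a constant effect is conditional on baseline being a repeated level, and its cost in power depends on the effect tested and on ρ. Bias from selective dropout is possible, but its size cannot be estimated from the article.

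**What to change.** Replace the method sentence with one defined model: a likelihood-based linear mixed model (SPSS MIXED) on the 1-, 3- and 6-month scores, with arm, visit, arm-by-visit and the baseline score of the same scale as covariate, and an unstructured covariance. Include every randomised participant with any post-baseline score, in the assigned arm. This still omits anyone with no follow-up score at all. If all randomised participants are to be kept, use multiple imputation before ANCOVA instead.

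State the primary contrast and time point, report the adjusted difference with its 95% confidence interval, and add one missing-not-at-random sensitivity analysis.

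The cost is a rewritten paragraph and slightly more analysis work. The software stays the same and no new data are needed, since baseline scores are already collected. The trade-off is reliance on missing at random, which the sensitivity analysis is there to probe.
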